## Protocol

Trial Registration
ISRCTN49726849 (registered on 27
^th^ October 2017).

Protocol Version 1.2: Date 9
^th^ October 2018.

### Justification for the study

This trial, designed to inform a key research gap, proposes targeted and appropriate antimicrobial treatment of children with severe malaria at greatest risk of bacterial co-infection. Incorporated in the design are experimental data to demonstrate that the mechanisms that azithromycin is targeting are biologically reasonable, that the dosing is providing the right exposure, and that there is a pharmacokinetic-pharmodynamic (PKPD) link between azithromycin exposure and the potential mechanisms for reducing both short-term and microbiological cure (seven-day) and longer-term mortality (28-day). Comparison with a control group will also enable us to identify whether antimicrobial treatment can be further targeted.

At present pharmacological data are lacking on the correct dosage of oral azithromycin for treatment of bacterial co-infection in severe malaria in African children. We will therefore conduct a Phase I/II trial comparing three doses of azithromycin: 10, 15 and 20 mg/kg (prescribed for feasibility by weight-bands) spanning the lowest to highest mg/kg doses demonstrated to be equally effective as parenteral treatment for other salmonellae infection
^
21
^.

### Our hypotheses

1. Azithromycin given to children once-daily for five days in addition to standard treatment of severe malaria (including anti-malarials) can provide adequate dosing in children admitted to hospital with severe malaria.

2. Children with severe malaria and culture-proven bacteraemia can be accurately identified using clinical criteria alone or in combination with a rapid diagnostic biomarker tests, in comparison with a control cohort of children hospitalized with severe malaria but not meeting Teule criteria, at low risk of bacterial co-infection.

## Objectives

### General objectives

Our principal objectives are to:

(i)   establish the appropriate dose of oral dispersible azithromycin as an antimicrobial treatment for children with severe malaria;

(ii)   investigate whether antibiotics can be targeted to those at greatest risk of bacterial co-infection using clinical criteria alone or in combination with a rapid diagnostic biomarker test.

### Specific objectives

(i)   To conduct a Phase I/II trial comparing three doses of azithromycin: 10, 15 and 20 mg/kg (prescribed for feasibility by weight-bands) spanning the lowest to highest mg/kg doses demonstrated to be equally effective as parenteral treatment for other salmonellae infection.

(ii)   To determine, via PKPD modelling, the optimal azithromycin dose in severe malaria, and investigate associations between azithromycin exposure and pathogen susceptibility (minimum inhibitory concentration, MIC) with treatment outcome. Outcome measures will consist of changes in C-reactive protein (CRP), a putative marker of sepsis at 72 hours (continuous) and microbiological cure (seven-day) (binary), alone and as a composite with seven-day survival, while providing preliminary data on longer-term survival (to day 90).

(iii)   To evaluate whether a combination of clinical, point-of-care diagnostic tests, and/or biomarkers can accurately identify the sub-group of severe malaria with culture-proven bacteraemia by comparison with a control cohort of children hospitalized with severe malaria but not meeting Teule criteria, at low risk of bacterial co-infection.

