## Abstract

**Background: **African children with severe malaria are susceptible to Gram-negative bacterial co-infection, largely non-typhoidal Salmonellae, leading to a substantially higher rates of in-hospital and post-discharge mortality than those without bacteraemia. Current evidence for treating co-infection is lacking, and there is no consensus on the dosage or length of treatment required. We therefore aimed to establish the appropriate dose of oral dispersible azithromycin as an antimicrobial treatment for children with severe malaria and to investigate whether antibiotics can be targeted to those at greatest risk of bacterial co-infection using clinical criteria alone or in combination with rapid diagnostic biomarker tests.

**Methods: **A Phase I/II open-label trial comparing three doses of azithromycin: 10, 15 and 20 mg/kg spanning the lowest to highest mg/kg doses previously demonstrated to be equally effective as parenteral treatment for other salmonellae infection. Children with the highest risk of bacterial infection will receive five days of azithromycin and followed for 90 days. We will generate relevant pharmacokinetic data by sparse sampling during dosing intervals. We will use population pharmacokinetic modelling to determine the optimal azithromycin dose in severe malaria and investigate azithromycin exposure to change in C-reactive protein, a putative marker of sepsis at 72 hours, and microbiological cure (seven-day), alone and as a composite with seven-day survival. We will also evaluate whether a combination of clinical, point-of-care diagnostic tests, and/or biomarkers can accurately identify the sub-group of severe malaria with culture-proven bacteraemia by comparison with a control cohort of children hospitalized with severe malaria at low risk of bacterial co-infection.

**Discussion**: We plan to study azithromycin because of its favourable microbiological spectrum, its inherent antimalarial and immunomodulatory properties and dosing and safety profile. This study will generate new data to inform the design and sample size for definitive Phase III trial evaluation.

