### Target population

Current recommendations indicate that antibiotics should be given to ‘all children with suspected severe malaria in areas of moderate and high transmission until a bacterial infection is excluded’
^
10
^. However, WHO definitions of severe malaria are very broad, incorporating high parasitaemia as a single criterion, and are thus applicable to a large proportion of paediatric admissions in such regions, with a relatively overall low case fatality (1–2%)
^
20
^, who are unlikely to benefit from antimicrobial therapy as a group. For this study (and in a future trial) we aim to target antibiotics to children with the highest risk of bacterial co-infection, meeting ‘Teule’ criteria
^
11
^: that is, with malaria (positive blood film or ParacheckTM rapid diagnostic test, RDT); temperature > 38°C or < 36°C; and ≥1 of prostration, respiratory distress, haemoglobin (Hb) <5g/dl or HIV. These criteria identified 85% of bacterial co-infections, with a three-fold higher mortality than children admitted with malaria without these criteria.

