## Sampling

### Sample size determination

A formal sample size was not calculated. Phase I/II trials are an important step in the assessment of new or existing interventions providing the first data on the feasibility of using a product in a new application. They assess the effect of products (how well they work), and the side effects they may have. They are not usually designed to compare superiority of different products or interventions.

The aim is to generate pilot efficacy data on the optimal azithromycin dose for children with severe malaria, which will inform the design of a later larger Phase III trial. The numbers required to address the trial objectives are therefore balanced against the exposure of children in these settings to a therapeutic intervention (dose) for which there are limited data to date.

The overall sample size for the trial will be 105 children randomised 1:1:1 to receive 10, 15 or 20mg/kg azithromycin (based on weight-bands). This is sufficient for the PKPD sampling and modelling to determine an optimal dose in children with severe malaria using change in CRP at 72 hours, and microbiological cure (seven-day) alone and with seven-day survival. This is under the assumption that 20% of enrolled children (meeting Teule severity criteria) will have bacteraemia and that 80% of these infections will be caused by NTS or other enteric gram-negative organisms based on previous research. 

Based on Monte Carlo simulations, we expect that all dose groups should reach the population reference target (adult) AUC24h of at least 3.4 h*mg/L
^
24
^, although there are no data on absorption in severe malaria, which is characterised by impaired gut function
^
25
^, hence the need for this pilot. Along with the 105 children with Teule criteria we will enrol 50 children meeting other inclusion criteria but without Teule criteria (and without any exclusion criteria) into the control group.

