### Biomarker and gut barrier function

In 105 trial participants and 50 children with controls (severe malaria without Teule criteria) we plan to investigate from admission samples the utility of a range of potential biomarkers including CRP, PCT
^
31,
32
^ and endotoxin
^
25
^, to identify whether any of the above markers, alone or in combination, can predict which at-risk children with severe malaria have bacterial co-infections to improve the sensitivity of clinical/laboratory criteria and enable antimicrobial therapy to be further targeted. We will investigate associations between pathological concentrations of these markers and clinical, parasitological and microbiological data in cases (meeting Teule criteria) and controls (not meeting Teule criteria) to test their accuracy for stratification in the main trial. The samples will also allow us to analyse markers of gut barrier dysfunction – a requisite for bacteraemia (intestinal fatty acid binding protein (I-FABP) and the ileal-bile acid binding protein (I-BABP) and establish whether these can accurately predict children with blood-culture proven bacteraemia alone or in combination with clinical criteria/RDTs. In addition, we will analyse the peripheral blood mononuclear cell transcriptome in a subset of children with and without bacterial co-infection to verify the significant changes in transcriptome we observed in a small pilot study of children with malaria and bacterial co-infection compared to children with malaria alone and to confirm observed changes on the cellular level in a second set of children
^
33
^. We will investigate whether changes in gene expression profile can be translated into rapid and affordable biological tests predicting children with bacterial co-infection with high specificity and sensitivity. This later analysis is subject to additional funding.

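### The stated comparator for marker accuracy is the Teule-negative cohort, which mixes bacteraemia with the selection criteria; culture-negative Teule-positive children should be the primary reference group

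*Protocol article*

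**What the plan says.** The comparator is stated consistently. Hypothesis 2 has bacteraemic children identified by clinical criteria, alone or with a rapid biomarker test, "in comparison with a control cohort of children hospitalized with severe malaria but not meeting Teule criteria, at low risk of bacterial co-infection". Specific objective (iii) asks whether clinical signs, biomarkers and bedside tests "can accurately identify the sub-group of severe malaria with culture-proven bacteraemia by comparison with a control cohort of children hospitalized with severe malaria but not" satisfying the Teule criteria. The Discussion repeats this, and the Abstract has "by comparison with a control cohort of children hospitalized with severe malaria at low risk of bacterial co-infection".

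The section Biomarker and gut barrier function covers the 105 trial participants and the 50 controls. It asks whether markers "can predict which at-risk children with severe malaria have bacterial co-infections to improve the sensitivity of clinical/laboratory criteria and enable antimicrobial therapy to be further", that is, more closely targeted. It then relates marker concentrations to microbiological, clinical and parasitological findings "in cases (meeting Teule criteria) and controls (not meeting Teule criteria) to test their accuracy for stratification in the main trial".

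The Teule criteria, as given under Target population, are malaria with "temperature > 38°C or < 36°C; and ≥1 of prostration, respiratory distress, haemoglobin (Hb) <5g/dl or HIV". Cases must meet them and controls must not. Under Sample size determination the plan assumes that "20% of enrolled children (meeting Teule severity criteria) will have bacteraemia".

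No section names Teule-positive children with a negative culture as the reference group for marker accuracy.

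**The concern.** The question and the comparator do not match. To target antibiotics further among at-risk children, a marker must separate Teule-positive children with bacteraemia from Teule-positive children without it. The matching null hypothesis is that the marker does not differ between those two groups. Comparing bacteraemic cases with Teule-negative controls tests a different null: that neither bacteraemia nor anything in the Teule criteria affects the marker. CRP, procalcitonin, endotoxin and gut-barrier markers could plausibly differ with fever, severity, anaemia or HIV without any effect of bacteraemia.

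The same contrast cannot show added value. Every bacteraemic case is Teule-positive and every control is Teule-negative, so the clinical criteria already separate the two groups completely. Yet the value of a marker in combination with those criteria is what hypothesis 2 asks about.

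The result is intended to inform stratification in a later trial. The Discussion says that trial may include a comparison with no antibiotics in children at minimal risk. Overstated accuracy would feed into how risk is assigned.

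**Working it through.** The plan gives no AUC, power or sample-size figure for marker accuracy, so there is none to reproduce. Its own inputs fix the group sizes.

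**Inputs from the protocol article**
- Cases: "The overall sample size for the trial will be 105 children randomised 1:1:1".
- Controls: 50 (Controls; Sample size determination).
- Bacteraemia among cases: 20% (Sample size determination).

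Bacteraemic cases: 105 × 0.20 = 21. Non-bacteraemic cases: 105 − 21 = 84. All non-bacteraemic children, assuming none of the controls is bacteraemic: 84 + 50 = 134.

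**Assumptions not in the documents.** The log-marker is normal with SD 1. All Teule-positive children are shifted by d SD. Bacteraemia adds b SD. Groups are compared by a two-sided rank test at 5%.

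**A marker with no relation to bacteraemia (b = 0)**
- Bacteraemic cases v controls: AUC = Φ(d/√2). For d = 0.5, Φ(0.354) = 0.64.
- Bacteraemic v non-bacteraemic cases: AUC = 0.50 for any d.
- Bacteraemic cases v all 134 pooled: AUC = (84 × 0.50 + 50 × Φ(d/√2))/134. For d = 0.5, (42 + 31.9)/134 = 0.55.

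False-signal rates come from simulation at these group sizes. Ranges show separate runs.

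| Assumed shift d (SD) | 21 v 50 controls: AUC, false signals | All 105 v 50 controls: false signals | 21 v 134 pooled: AUC, false signals | 21 v 84 within cases: AUC, false signals |
|---|---|---|---|---|
| 0.25 | 0.57, 15% | 29% | 0.53, 6–8% | 0.50, about 5% |
| 0.5 | 0.64, 43–46% | 81% | 0.55, 11–12% | 0.50, about 5% |
| 0.75 | 0.70, 78% | 99% | 0.58, 19% | 0.50, about 5% |
| 1.0 | 0.76, 96% | 100% | 0.60, 29–30% | 0.50, about 5% |

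**A marker with a real effect (b = 0.7, d = 0.5)**
- Within cases: Φ(0.7/√2) = 0.69.
- Against controls: Φ(1.2/√2) = 0.80.
- Pooled: (84 × 0.69 + 50 × 0.80)/134 = 0.73.

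**A check that needs no assumed shift.** Treat the Teule criteria themselves as the test. Bacteraemic cases against the control cohort give sensitivity 21/21 and specificity 50/50, both 100% by construction. On the plan's own 20%, however, 84 of 105 Teule-positive children have no bacteraemia. Specificity against all 134 is 50/134 = 37%, and that figure is itself set by the enrolment quotas.

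**Is the within-case contrast workable?** With 21 v 84, power is 79% for a 0.7 SD effect (AUC 0.69). The 95% half-width (Hanley–McNeil) is about 0.13 at AUC 0.70 and 0.12 at AUC 0.80. An uninformative marker would have an interval of about 0.36 to 0.64.

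**The case against.** A reader might infer that the 84 non-bacteraemic cases are left out of the marker analysis. The documents do not support that. The sub-study text covers all 155 children, cites microbiological data, and includes prediction of culture-proven bacteraemia. Table 3 schedules the day-0 blood culture without the restriction to cases that it places on the day-7 culture. An analysis of all 155 children against culture result is a fair reading, and a within-case analysis is not ruled out. Under the pooled reading the bias is much smaller, as the table shows. That stands, and it limits the size of the point. It does not remove it, because the pooled AUC still mixes a comparison within cases with one across Teule status.

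A second tempting inference is that the controls serve no purpose. The sub-study also aims to improve the sensitivity of the clinical criteria, and hypothesis 2 includes clinical criteria alone. All cases meet Teule, so a within-case analysis cannot address either. The plan describes controls as low risk, not free of bacteraemia, and says the criteria identify 85% of co-infections, so some fall outside them. Once culture-positive controls are counted as bacteraemic, the perfect separation above no longer holds. This stands too, and is why the controls need a defined secondary role.

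Finally, the sub-study is exploratory, the trial has no formal sample size, and an analysis plan not shown here may specify the model. The model can be left to that plan. The comparator is different: the hypothesis and objective already state it, and it does not fit the sub-study's question.

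**Conclusion.** The point holds for the comparator as stated in hypothesis 2, specific objective (iii), the Abstract and the Discussion, and for the Teule-status framing in the sub-study section. If followed as written, it confounds bacteraemia with the criteria that select cases. For an assumed 0.5 SD Teule shift and no bacteraemia effect, the apparent AUC is about 0.64 with about 45% false signals, against 0.50 and 5% within cases. Pooling all non-bacteraemic children reduces this to about 0.55 and 12%.

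The direction follows from the design whenever a marker rises with the Teule features. The size depends on the assumed shift, which the documents do not give, and on assuming no bacteraemia among controls. It is not shown that the sponsor will omit a within-case analysis or that any particular marker will be misjudged.

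One related inconsistency could change the size. Treatment allocation describes the comparator cohort as having non-severe malaria, whereas the objectives and the Controls section say severe malaria. These passages must be reconciled; a non-severe cohort would widen the severity gap.

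**What to change.** In hypothesis 2, specific objective (iii) and the biomarker section:

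- Define the reference standard as the admission blood culture result, not Teule status.
- Make bacteraemic versus non-bacteraemic children within the 105 Teule-positive cases (about 21 v 84) the primary contrast, both for marker accuracy (AUC, sensitivity and specificity with 95% intervals) and for what a marker adds to clinical criteria.
- Keep the 50 Teule-negative controls for a secondary analysis by culture result, with Teule status in the model, addressing the clinical criteria and any bacteraemia they miss.
- Do not report cases versus controls, or bacteraemic cases versus controls, as accuracy for bacteraemia.
- Carry the wording through to the Abstract and Discussion.

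The cost is wording and analysis. The admission cultures and samples are already in the schedule, and the article says the data are still being analysed. The downside is that reported accuracy will be less favourable and will rest on about 21 bacteraemic children, with intervals of roughly ±0.12 to ±0.13 on the AUC.

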## Methods

### Study site

The trial will be conducted in Mbale Regional Referral Hospital (MRRH), Eastern Uganda, where we already have an on-going collaborations
^
22,
23
^, in an area with hyperendemic malaria and paediatric admissions of >20,000/year, approximately 50% with malaria parasitaemia. MRRH is now an established research hub of the KEMRI-Oxford-Wellcome Trust Major Overseas Programme, assisted by trial, data and laboratory management from Kilifi, Kenya.

### Study design

A Phase I/II open-label trial comparing three doses of azithromycin: 10, 15 and 20 mg/kg (prescribed for feasibility by weight-bands) spanning the lowest to highest mg/kg doses demonstrated to be equally effective as parenteral treatment for other salmonellae infection.

## Study populations

Children will be considered eligible for enrolment in this trial if they fulfil all the inclusion criteria and none of the exclusion criteria. 

### Inclusion criteria

*Cases:*

105 children aged six months to 12 years at admission to hospital with
*P. falciparum* malaria (on either blood film or ParacheckTM RDT) and all of the following:

i) Axillary temperature >38°C or <36°C.

ii) Teule severity criteria
^
11
^: any one of the following: prostration; respiratory distress; severe anaemia (haemoglobin<5g/dL) or HIV infection.

iii) Parents willing/able to provide consent.

### Controls

The control cohort of children (n=50) are those hospitalised with severe malaria but not meeting Teule criteria (i.e., low risk of bacterial co-infection) whose parents are willing/able to provide consent.

### Exclusion criteria (cases only)

Major contraindications to azithromycin, e.g. strong existing clinical diagnosis of QT-prolongation. Concomitant use of interacting drugs: drugs that may cause QT-prolongation or drugs that may cause a pharmacokinetic interaction with azithromycin, like strong CYP3A/P-GP inducers and concomitantly administered antacids. 

## Sampling

### Sample size determination

A formal sample size was not calculated. Phase I/II trials are an important step in the assessment of new or existing interventions providing the first data on the feasibility of using a product in a new application. They assess the effect of products (how well they work), and the side effects they may have. They are not usually designed to compare superiority of different products or interventions.

The aim is to generate pilot efficacy data on the optimal azithromycin dose for children with severe malaria, which will inform the design of a later larger Phase III trial. The numbers required to address the trial objectives are therefore balanced against the exposure of children in these settings to a therapeutic intervention (dose) for which there are limited data to date.

The overall sample size for the trial will be 105 children randomised 1:1:1 to receive 10, 15 or 20mg/kg azithromycin (based on weight-bands). This is sufficient for the PKPD sampling and modelling to determine an optimal dose in children with severe malaria using change in CRP at 72 hours, and microbiological cure (seven-day) alone and with seven-day survival. This is under the assumption that 20% of enrolled children (meeting Teule severity criteria) will have bacteraemia and that 80% of these infections will be caused by NTS or other enteric gram-negative organisms based on previous research. 

Based on Monte Carlo simulations, we expect that all dose groups should reach the population reference target (adult) AUC24h of at least 3.4 h*mg/L
^
24
^, although there are no data on absorption in severe malaria, which is characterised by impaired gut function
^
25
^, hence the need for this pilot. Along with the 105 children with Teule criteria we will enrol 50 children meeting other inclusion criteria but without Teule criteria (and without any exclusion criteria) into the control group.

